##### Patients with a hospital acquired complication (H_2_)

Rate per 1000 patient days of respiratory (HAC03) and healthcare-associated infections (HAC06), the leading preventable HACs influenced by nursing care. Nationally, HACs are reported by facility per 1000 patient days. In NSW, the study sites are above the state average of 2.17:1000 patient days. The secondary outcomes are hospital resource use and costs (health service perspective) and the rate of all HACs.

##### Patients subjected to events causing harm or near miss (H_3_)

Rate of Harm Score 1 per 1000 admissions. Harm scores range from 1 (death) to 4 (near miss) based on the severity of outcome and additional post-incident treatment requirements. In 2023, the study sites had a total of 14 Harm Score 1, 97 Harm Score 2, and 1829 Harm Score 3 events. The secondary outcomes are the rate of harms per 1000 for 2, 3 and 4.

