##### Hypotheses

The evaluation of the intervention will test the seven hypotheses listed in Table 1.

**Table 1 Tab1:** List of the seven primary hypotheses to be tested throughout the implementation and evaluation of HIRAID® Inpatient

Hypothesis	Implementation of HIRAID® Inpatient will result in a…
H_1_	…20% reduction in rapid response team activation due to preventable patient deterioration
H_2_	…10% reduction in Hospital Acquired Complications (HAC03 and HAC06)
H_3_	…20% reduction in events causing patient harm or near miss
H_4_	…10% improvement in experience of care reported by patient or carer
H_5_	…10% increase in quality of nurse communication and handover
H_6_	…healthcare resource use and cost estimates that will lead to favourable cost-effectiveness estimates
H_7_	…high fidelity (80%) implementation

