#### Outcomes

##### Patients with a preventable clinical deterioration (H_1_)

Rate per 1000 admissions of preventable patient deterioration calls (RRT calls) related to nursing assessment and management, observation and monitoring. RRT activation is already recorded in local databases and will be used to identify patients for medical record review, independent assessment and verification of causal factors [38]. Secondary outcome is transfer to a higher level of care (e.g. to Intensive Care Unit) (Table 3).

**Table 3 Tab3:** Summary of HIRAID® Inpatient outcome measure, data collection sources and measurement timepoints

Outcome	Outcome description	Outcome measure	Data analysis	Data source	Control (pre)	Implementation	Intervention (post)
Patient health outcomes							
Outcome 1 (H1)	Nursing-related preventable clinical deterioration	Incidence of clinical deterioration events related to nursing assessment and care	*Descriptive approach, generalised linear model (GLM) approach	Patient deterioration database, eMR records	✓	-	✓
Outcome 2 (H1)	Transfer to higher level care	Incidence of patients transferred to higher level care	*Descriptive approach, GLM approach	Patient deterioration database, eMR records	✓	-	✓
Outcome 3 (H2)	Hospital Acquired Complications (HACs) influenced by nursing care	Incidence of patient days with respiratory complication (HAC03), and/or healthcare-associated infections (HAC06)	*Descriptive approach, GLM approach	Health District data collections, Performance Planning Unit (PPU) database, eMR records	✓	-	✓
Outcome 4 (H2)	HACs influenced by nursing care–health service perspective	Incidence of hospital resource use and costs	*Descriptive approach, GLM approach	Health District data collections, PPU database, eMR records	✓	-	✓
Outcome 5 (H2)	HACs influenced by nursing care	Rate of all other HACs (not HAC03 and HAC06)	*Descriptive approach, GLM approach	Health District data collections, PPU database, eMR records	✓	-	✓
Outcome 6 (H3)	Events that cause patient harm or near miss	Incidence/proportion of adverse patient harm or near miss events	*Descriptive approach, GLM approach	Health District data collections, PPU database, eMR records	✓	-	✓
Patient and carer experience outcomes							

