#### Sample size

Sample sizes were calculated for each of the hypotheses. Hypotheses H1, H2, H3, and H6 sample size estimations were conducted collectively, as they will use medical record and cost data from relevant systems for the period of 1 st July 2026 to 1 st December 2027 (Table 4—shaded grey). To maximise the study’s power in detecting true differences, should they exist, the largest sample size estimation is reported and will be used. Sample sizes were calculated with an assumed intra-class correlation of 3%, 5% significance (two-tailed) and 80% power, and applying Woertman’s SW design estimate approach [48]. These sample sizes have been calculated using the most recent data from the study sites and/or previous work by the investigators in this field. To evaluate implementation fidelity HIRAID® facilitators (CNCs/CNEs) employed to assist with education and roll out will be invited to participate in the evaluation of implementation fidelity. The number of staff to be involved in this process will be determined by each LHD.

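### The H3 outcome text leads with deaths only (Harm Score 1), while Tables 1 and 3 count all harm and near-miss events; if deaths are meant, the stated 80% power is about 4–7%

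*Protocol article*

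**What the plan says.** Three places in the protocol article define H3.

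- **Hypotheses, Table 1** (whose title calls all seven hypotheses primary): a "20% reduction in events causing patient harm or near miss".
- **Outcomes, Table 3, Outcome 6 (H3):** "Incidence/proportion of adverse patient harm or near miss events".
- **Outcomes, H3 paragraph:** "Rate of Harm Score 1 per 1000 admissions". The scale runs from 1 for death to 4 for near miss. It then states: "The secondary outcomes are the rate of harms per 1000 for 2, 3 and 4".

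The H3 paragraph also gives the baseline: in 2023 "the study sites had a total of 14 Harm Score 1, 97 Harm Score 2, and 1829 Harm Score 3 events". It gives no count for Score 4.

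The Sample size section says that a sample size was calculated for every hypothesis, that H1, H2, H3 and H6 were sized together with the largest result used, and that "Sample sizes were calculated with an assumed intra-class correlation of 3%, 5% significance (two-tailed) and 80% power", with Woertman's stepped-wedge approach. The figures for each hypothesis are in Table 4, which is an image and is not available here.

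**The concern.** The H3 paragraph does not use the word primary for Score 1. But it names one outcome and then lists the others as secondary, as the H1 and H2 paragraphs do, so the natural reading is that Score 1 decides H3. Near misses then appear in the hypothesis but only as a secondary outcome.

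Two things are at stake. First, with two candidate outcomes on record, the choice between them could be made after the data are seen. Second, the candidate in the H3 paragraph is so rare that a 20% reduction cannot be detected. A null result would say almost nothing, and a nominally significant one would rest on a handful of deaths.

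**Working it through.** **The plan's own figure.** The 80% cannot be reproduced, because the H3 inputs are in Table 4. It can be tested against the most data the design can give: every admission in the control and intervention periods.

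**Inputs**

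- Admissions: 48,609 a year (Table 2), or 48,609/12 = 4,050.75 a month.
- Score 1 events: 14 a year, so the rate is 14/48,609 = 0.288 per 1000.
- Effect: 20% relative reduction (Table 1). Two-sided 5% (Sample size).
- Layout: the Fig. 3 caption gives 3–12 months control, 3 months transition and 3–12 months intervention. I assume equal 3-month steps over 18 months. Control time is then 3+6+9+12 = 30 cluster-months, and intervention time is the same.
- The 14 events are assumed to belong to the study wards.

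**Expected events**

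- Admissions per condition: 4,050.75 × 30/4 = 30,381.
- Control: 14/12 × 7.5 = 8.75. Intervention: 0.8 × 8.75 = 7.0.

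**Power for Score 1**

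- Normal approximation: z = (8.75 − 7.0)/√15.75 = 0.441. Power = Φ(0.441 − 1.96) + Φ(−0.441 − 1.96) = 0.064 + 0.008 = 7.3%.
- Wald test on the log rate ratio: SE = √(1/8.75 + 1/7.0) = 0.507; z = 0.223/0.507 = 0.440; power 7.2%.
- Exact conditional test of two Poisson counts: 4.3%.
- Poisson model with cluster and period effects, over all 24 cluster orders: 5.4%.
- Woertman design effect with ICC 0.03: 4.3%.
- If the window ends on 1 December 2027, as the Sample size section says (about 17 months), expected events are 8.2 against 6.5, and the exact test gives 4.1%.

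**Size needed for 80%**

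n per condition = (1.96 + 0.8416)² × (λ + 0.8λ)/(0.2λ)², with λ = 0.000288. This gives 7.849 × 1.8/(0.04 × 0.000288) ≈ 1.23 million admissions. That is about 40 times the 30,381 available, and for both conditions about 2.45 million/48,609 ≈ 50 years of study-ward admissions.

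**The broader outcome**

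Scores 1–3: 14 + 97 + 1,829 = 1,940 a year, or 39.9 per 1000.

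| Method | Power for a 20% reduction, Scores 1–3 |
|---|---|
| Simple comparison, no clustering or time | above 99% |
| Woertman design effect | about 84% |
| Poisson, cluster and period effects, transition quarter excluded | 56–59% over the 24 orders (SE of log rate ratio 0.102–0.106) |

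For the Woertman row, with k = 4 steps, b = t = 1, ICC 0.03 and 60,761/20 = 3,038 admissions per cluster-period, the design effect is 0.646. The equivalent simple trial has 60,761/(5 × 0.646)/2 ≈ 9,409 per condition.

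The last two rows differ mainly because of the transition quarter. The same Poisson model with equal clusters, five periods, no transition gap and the same total admissions gives about 81%.

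**The case against.** The strongest reply is that the protocol nowhere says that 80% power applies to deaths. The Sample size section speaks of H3, Table 1 ties the 20% to all harm or near-miss events, and Table 4 is not available. The sizing may have used the broad outcome, for which the cited Woertman approach gives about 84% on Scores 1–3. This stands. A reader might infer that the sponsor claimed 80% power for Score 1; the documents do not support that, and the 4–7% is conditional on Score 1 being the H3 outcome.

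It can also be said that primary is only implied. The H4 paragraph uses the word and the H3 paragraph does not, and the heading of the H3 paragraph is itself the broad one. A drafting slip is as plausible as a deliberate choice of deaths. This also stands, but it does not remove the conflict.

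A reader might go further and conclude that H3 cannot be answered at all. That is too strong: Outcome 6 in Table 3 covers all harm or near-miss events, and Scores 2, 3 and 4 are each listed as secondary, so H3 as worded in Table 1 would still be estimated.

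Finally, which severities should define H3 is partly the sponsor's choice, and a combined rate is not free of trouble: with period adjustment its power is also below 80%.

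**Conclusion.** The point holds as an inconsistency with a conditional consequence for power. The H3 paragraph and Tables 1 and 3 give different outcomes for one primary hypothesis, and this must be settled before data are seen. If Score 1 is the outcome, the 80% cannot be right: power for a 20% reduction is about 4–7% by every two-sided method tried, and no entry in Table 4 could change this, because the calculation already uses all admissions. If the broad outcome was sized, the error lies in the H3 paragraph, and the 80% is compatible with the Woertman calculation but not with a period-adjusted model on the layout with its transition quarter.

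The figures assume equal 3-month steps and that the 2023 counts come from the study wards. The text says study sites. If the counts are hospital-wide, power is lower for Score 1 and for the combined rate alike.

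**What to change.** - Bring the H3 paragraph into line with Tables 1 and 3: make the combined harm rate per 1000 admissions the H3 primary outcome. Use Scores 1–3, or Scores 1–4 once a Score 4 baseline count is given.
- Report Scores 1 and 2 separately and descriptively.
- State which outcome Table 4 sized for H3, and whether the 2023 counts are for the study wards or the whole hospitals.
- Restate the H3 power for the chosen outcome, under a model with period effects and the transition quarter excluded. On present figures for Scores 1–3 this is about 56–59%, against about 84% under Woertman.

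The cost is wording, one power calculation and a registry update, all possible before the planned start in July 2026. The downside is that Score 3 makes up 1,829/1,940 = 94% of the combined count, so the result would mostly describe the less severe events and the components must be shown beside it.

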##### Inpatients (or their carers) experience with nursing care (H_4_)

The two validated instruments, the Schmidt’s Perceptions of Nursing Care Survey [39] and the Australian Hospital Patient Experience Question Set (AHPEQS) [40], will be used to measure patient perceptions and experience of nursing care. The resources will be translated into the top five languages for each cluster to enable inclusion of patients who do not speak English [41]. Remuneration will be offered per the NSW Classification and Remuneration Guidelines for NSW Government Boards and Committees ($20 voucher suitable for rural/regional participants) and as a strategy known to increase response rates. The primary outcome is the patient (or their carers’) experience of nursing care. The secondary outcomes include the following: overall care experience; Schmidt’s subscales, including Seeing the Individual Patient, Explaining, Responding, Watching Over; and patient complaints relating to nursing care [39].

##### Nursing documentation (H_5_)

(i) Experiences with the quality of information transfer from nursing staff during handover, and (ii) nurse confidence in patient assessment and escalation of care will be measured through a validated electronic survey of nurses, medical and allied health staff [42]. Clear, coherent and comprehensive communication is essential for patient safety and collaboration [43]. (iii) Documentation quality will be evaluated using the D-catch tool [44] and records checked for sufficiently linguistically correct, legible, and using the correct terminology to meet all medico-legal requirements [45]. A sub-sample of patient records from H_1_ will be used.

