Outcome 7 (H4)	Patient and carer perceptions and experience of nursing care	Average score reported on the Australian Hospital Patient experience question set and Schmidt's Perceptions of Nursing Care Survey	*Descriptive approach, logistic regression for binary outcome variables, linear regression for continuous outcome variables	eMR records, patient/carer satisfaction surveys, patient complaints	✓	-	✓
Outcome 8 (H4)	Patient and carer overall care experience and patient complaints relating to nursing care	Average scare reported on remainder Schmidt’s Perceptions of Nursing Care Survey, and content analysis of complaints	*Descriptive approach, logistic regression for binary outcome variables, linear regression for continuous outcome variables	eMR records, patient/carer satisfaction surveys, Patient complaints	✓	-	✓
Staff experience and capability outcomes							
Outcome 9 (H5)	Staff satisfaction with communication (handover)	Average score on Staff Satisfaction with Handover Surveys (Inter-professional communication)	*Descriptive approach, multiple linear regression modelling, logistic regression for binary outcome variables, linear regression for continuous outcome variables	Nursing/allied health/medical staff surveys	✓	-	✓
Outcome 10 (H5)	Nurse confidence in patient assessment and escalation of care	Average score on Confidence with communication survey	*Descriptive approach, multiple linear regression modelling	Nursing/allied health/medical staff surveys	✓	-	✓
Outcome 11 (H5)	Quality and quantity of nursing documentation	Average score of modified D-catch tool	*Descriptive approach, multiple linear regression modelling	Nursing/allied health/medical staff surveys	✓	-	✓
System-level and Implementation outcomes							
Outcome 12 (H6)	Acute treatment costs	Average of incremental net health service cost per rapid response team calls avoided	*Descriptive approach, Extrapolation modelling, time horizon modelling, Discrete event simulation (stochastic)	Health District data collections, PPU(Costs) database	✓	-	✓
Outcome 13 (H7)	Implementation fidelity	Outcomes reported on the implementation fidelity surveys and nurse interviews	*Descriptive approach, process evaluation, structured fidelity scoring	Audits, Nursing staff interviews, Nurse facilitator survey	-	✓	✓

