##### Medical and allied health staff survey

Medical and allied health staff satisfaction with nurse communication (control and intervention). Staff satisfaction with RN communication and quality of information received during handover, using a previously validated eight-item, 11-point Likert scale, plus five yes/no questions instrument [31]. The opinion of permanently employed medical and allied health staff is sought as a component of HIRAID® Inpatient communication. A unique identifier will be generated by responders to enable post-intervention matching. The survey will be distributed electronically and used to inform H5 (improved quality of nursing communication and handover).

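### H5 is one primary hypothesis carried by three outcomes, none named as the deciding one, and its outcome section is headed with a different construct from Table 1

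*Protocol article*

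**What the plan says.** Table 1 of the protocol article is captioned "List of the seven primary hypotheses to be tested throughout the implementation and evaluation of HIRAID® Inpatient", and its fifth entry is a "10% increase in quality of nurse communication and handover". That is one hypothesis with one target.

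The Phase 3 outcome section for H5 is headed as nursing documentation and lists three measures:

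- (i) "Experiences with the quality of information transfer from nursing staff during handover", by staff survey;
- (ii) in its words, "ii) nurse confidence in patient assessment and escalation of care will be measured through a validated electronic survey";
- (iii) in its words, "iii) Documentation quality will be evaluated using the D-catch tool", applied to a sub-sample of the H1 records.

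Table 3 carries these as Outcome 9 (the handover satisfaction score), Outcome 10, "Nurse confidence in patient assessment and escalation of care", and Outcome 11, "Quality and quantity of nursing documentation". All three bear the H5 tag. Neither the section nor the table ranks them or says whether one, all or a particular one must succeed.

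The survey section for medical and allied health staff says that its handover instrument is "used to inform H5 (improved quality of nursing communication and handover").

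The Sample size section assumes two-tailed 5% significance and 80% power. The Statistical methods section sets alpha at 0.05 and does not divide it between measures.

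**The concern.** A primary hypothesis needs one outcome, or one stated rule over several outcomes, that decides it. H1 to H4 have this structure: each outcome section sets secondary outcomes apart from the main one. H5 does not, and the text supports more than one reading. Someone starting from Table 1 would take the handover score as decisive. Someone starting from the section heading would take D-Catch.

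The three measures can disagree, and the plan would then support opposite conclusions about H5. The sharpest case is a rise in self-rated confidence with no change in handover or documentation. Nothing written prevents that from being reported as H5 met. Yet the Methodological considerations section gives nurses' perceived confidence as its own example of a self-report measure at risk of bias, because staff know when they have moved to the intervention.

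The 10% target is also tied to no scale, although the instruments differ. According to the nursing staff survey section, confidence has 14 items on an 11-point scale, and the handover instrument has eight 11-point items plus five yes/no questions. D-Catch is a separate record audit.

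This issue lies within one hypothesis and is distinct from multiplicity across the seven.

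**Working it through.** **Inputs from the protocol article.** Three outcomes tagged H5 (Table 3); two-sided alpha 0.05 and power 80% (Sample size); alpha 0.05 without a split (Statistical methods).

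**Inputs assumed.** The correlation ρ between the three test statistics is not given. It is taken as common to all pairs and varied. The rule for claiming H5 is not given either, so two rules are tried. The article states no error rate for H5 as a set, and Table 4 is not shown, so there is no figure of its own to reproduce beyond the single-test 5%.

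**Rule A: H5 is claimed if any one outcome is significant, with no true effect.**

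Independent tests, both tails: 1 − (1 − 0.05)³ = 1 − 0.857375 = 0.1426.

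Independent tests, favourable tail only: 1 − (1 − 0.025)³ = 1 − 0.926859 = 0.0731.

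For correlated tests, write each statistic as Zⱼ = √ρ·U + √(1−ρ)·Eⱼ, with U and Eⱼ independent standard normals, and c = 1.96. Then

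P(at least one |Z| > c) = 1 − ∫ [Φ((c − √ρ·u)/√(1−ρ)) − Φ((−c − √ρ·u)/√(1−ρ))]³ φ(u) du.

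The favourable-tail version drops the second Φ term. Numerical integration gives:

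| ρ (assumed) | Any significant, both tails | False improvement only |
|---|---|---|
| 0 | 14.3% | 7.3% |
| 0.5 | 12.5% | 6.3% |
| 0.8 | 9.8% | 4.9% |
| 0.9 | 8.4% | 4.2% |
| One named outcome | 5.0% | 2.5% |

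From ρ = 0 to 0.8, either column is about 2 to 2.9 times its single-outcome value (14.3/5.0 = 2.9 and 9.8/5.0 = 2.0; 7.3/2.5 = 2.9 and 4.9/2.5 = 2.0).

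**Rule B: H5 is claimed only if all three outcomes are significant in the favourable direction, each with 80% power.**

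Independent: 0.80³ = 0.512. For correlated statistics the mean shift is 1.96 + 0.84 = 2.80, and the same integration gives 61% at ρ = 0.5 and 69% at ρ = 0.8.

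**With one deciding outcome.** The error rate for H5 returns to 5% two-sided, and its power is whatever that outcome was sized for.

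**The case against.** The strongest reply is that the article nowhere says H5 is met when any one measure is significant. That is correct. The error rates describe a permitted reading, not a stated rule, and they rest on assumed correlations. H5 is also directional, so the two-sided figures count significant worsening as a false claim; the favourable-tail column is the fairer measure of wrongly declaring improvement. A requirement that the observed change reach 10% would lower the rates further, but no such requirement is stated as a decision rule.

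A reader might infer that confidence and documentation fall outside H5 altogether. The documents do not support that. Table 1 names nurse communication as well as handover, Outcome 10 is scored on a confidence-with-communication survey, and documentation is written communication. What holds is narrower: neither measures handover quality.

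A reader might also infer that Outcome 9 is the only defensible choice. It too is an unblinded staff self-report, completed partly by the same nurses. Its instrument has several items and goes to nursing, medical and allied health staff. D-Catch has the advantage that, under the Blinding section, researchers assessing nursing documentation remain blinded.

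Finally, Table 4 and any analysis plan are not shown. Table 4 may reveal which measure H5 was sized on, and alpha allocation is often left to an analysis plan. Neither removes the point. A sample-size row is not a decision rule, and the article itself sets main apart from secondary outcomes for H1 to H4. The contrast is not perfect, since the main H4 outcome draws on two instruments and H6 and H7 carry no such labels.

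**Conclusion.** The point holds in this form: a single primary hypothesis has three outcomes and no named deciding one, and the section heading and Table 1 disagree about its subject. That much rests on the text alone.

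The size is conditional. Under an any-one rule, the false-positive rate is about 14% to 10% against 5%, or about 7% to 5% against 2.5% for false improvement, at assumed correlations from 0 to 0.8. Under an all-three rule, power is about 51% to 69%, provided each outcome really has 80%, which cannot be checked without Table 4. Neither rule delivers the stated 5% and 80% for H5.

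It should be put right before data collection. It does not threaten the other hypotheses.

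**What to change.** In the H5 outcome section and Table 3, name one deciding outcome for H5, and align the section heading with Table 1. Recruitment is scheduled to begin on 1 July 2026, so this can be done before any data are collected.

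- Outcome 9 is the best match to Table 1 and to the medical and allied health survey section. It needs to be fixed as one overall handover score from a stated respondent group; otherwise several tests remain inside it.
- If the investigators prefer the D-Catch score because its assessment is blinded, H5 in Table 1 should be reworded to match.
- Attach the 10% target to the chosen score only.
- Label the other two outcomes secondary and state that neither, self-rated confidence in particular, can establish H5 alone.

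The change is one of wording, and all three measures are already planned. The investigators should check that the H5 sample size in Table 4 was derived for the chosen outcome. The cost is that H5 can no longer be claimed on a secondary measure. If Outcome 9 is chosen, the deciding outcome is an unblinded self-report, so D-Catch should be reported beside it as the blinded secondary.

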##### Deteriorating patient database and electronic medical record (eMR)

Patient’s that have a rapid response call activated while an inpatient in a study ward will be identified through existing site rapid response databases. In addition to reviewing the quality of documentation using the audit tool (Supplement 1), these records will be reviewed to identify causal factors associated with the rapid response call and determine if suboptimal inpatient nursing care was a precursor, for example, unreported or delayed reporting (> 30 min) of vital sign abnormalities fulfilling hospital criteria. The instrument (Supplement 1) outlines the variables collected and incorporates the validated Human Factors Classification Framework for patient safety [38], which considers equipment, work environment, staff action and patient factors. To ensure consistent data collection, research nurses assessing clinical documentation and patient deterioration events will complete data collection on a minimum sample of 10 duplicate records to complete inter-rater reliability at commencement. Ongoing audits will maintain data collection consistency.

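### Documentation quality is scored only on records of patients with a rapid response call, a set that the intervention is expected to change

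*Protocol article*

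**What the plan says.** Table 1 of the protocol article lists H5 among seven primary hypotheses: "10% increase in quality of nurse communication and handover". The outcome section on nursing documentation (H5) gives it three measures: experience of information transfer at handover, nurse confidence, and documentation quality scored with the D-Catch tool. None is marked as the main one. For the third, the section adds: "A sub-sample of patient records from H_1_ will be used".

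Two sections show what an H1 record is. The H1 outcome section says: "RRT activation is already recorded in local databases and will be used to identify patients for medical record review". The section on the deteriorating patient database and eMR says that patients "that have a rapid response call activated while an inpatient in a study ward will be identified through existing site rapid response databases", and continues: "In addition to reviewing the quality of documentation using the audit tool (Supplement 1), these records will be reviewed to identify causal factors". Reviewers of these records also "determine if suboptimal inpatient nursing care was a precursor, for example, unreported or delayed reporting (> 30 min) of vital sign abnormalities".

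Table 1 states the expected effect under H1: "20% reduction in rapid response team activation due to preventable patient deterioration".

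Table 3, Outcome 11, gives the measure as "Average score of modified D-catch tool", but its data-source column lists staff surveys, not patient records.

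No other sample is named for the D-Catch score. The fortnightly documentation audits under Supporting materials serve to track implementation.

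**The concern.** The D-Catch comparison is conditioned on an event, the RRT call, that the intervention is designed to affect. If preventable calls fall, the intervention-period sample holds a smaller share of them. If their records are on average poorer, the mean score rises even though no nurse documents differently. Better escalation could also add calls, which changes the sample again. The Rationale section reports that HIRAID® in emergency departments reduced failure to escalate, so this is a plausible second route.

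Two things are at stake. The first is whether a difference in mean score can be read as a change in documentation practice. The second is scope: the framework is for all patients on the study wards (48,609 admissions a year in Table 2), while the score would describe only those who deteriorated to a call.

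**Working it through.** The document states no figure for this effect, and the content of Table 4 is not shown, so there is nothing to reproduce. The check asks how far the mean score moves through composition alone, with no true change in documentation in either type of call.

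**Inputs**
- Cut in preventable calls: 20% (Table 1, H1).
- H5 target: 10% (Table 1), taken here as applying to the mean D-Catch score.
- Preventable share of RRT calls, p: not given. Assumed 20–60% on the SD scale and 10–90% on the relative scale.
- Documentation gap between preventable and other calls: not given. Assumed 1 SD on the SD scale, and a deficit d of 10–50% on the relative scale.

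**Shift in composition.** With a 20% cut and nothing else, the preventable share becomes p' = 0.8p / (1 − 0.2p).

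| p | p' | Fall in share | Spurious gain at a 1 SD gap |
|---|---|---|---|
| 0.2 | 0.16/0.96 = 0.167 | 3.3 points | 0.033 SD |
| 0.4 | 0.32/0.92 = 0.348 | 5.2 points | 0.052 SD |
| 0.6 | 0.48/0.88 = 0.545 | 5.5 points | 0.055 SD |

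The fall peaks at 5.6 points, near p = 0.53, so the result is not sensitive to p in the middle of the range. It scales directly with the assumed gap.

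**Against the 10% target.** The document as shown gives no D-Catch SD, so SD units cannot be turned into per cent. On a relative scale, set the mean score for other calls to 1 and for preventable calls to 1 − d. The apparent gain is (1 − p'd)/(1 − pd) − 1.
- p = 0.3, d = 20%: p' = 0.255, and 0.9489/0.94 − 1 = +0.95%.
- p = 0.5, d = 30%: p' = 0.444, and 0.8667/0.85 − 1 = +1.96%.
- Largest value over all p: +0.6%, +1.2%, +2.0% and +3.9% for d = 10%, 20%, 30% and 50%.

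**Can the sign reverse?** Two patterns were tried.
- The prevented calls are those with the better records. Let half of preventable calls have no deficit and half a 30% deficit, with the cut falling only on the first half. At p = 0.5 the mean goes from 0.925 to 0.825/0.9 = 0.917, a change of −0.9%. At p = 0.3 the change is −0.3%.
- Better escalation adds calls, equal to 10% of baseline calls, from poorly documented patients who would not previously have been escalated. At p = 0.3 the poorly documented share becomes (0.24 + 0.10)/(0.94 + 0.10) = 0.327, up from 0.30. The mean changes by −0.6% for d = 20% and by −0.9% for d = 30%. With only 5% added calls the change stays positive, at +0.15% and +0.23%.

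**After the fix.** If records are sampled without regard to RRT calls, this composition shift is zero.

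**The case against.** The strongest reply has four parts.

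1. *The direction is not established.* This stands. A reader might infer that the design always favours the intervention. That follows only if preventable calls have poorer records and any added calls are well recorded, and the document states neither. The reversals above show that other patterns are possible. What supports the likelier direction is that preventability is judged partly from what nurses reported and when, so poorer records in that group are plausible.

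2. *The size is modest.* This stands too. A reader might reach larger figures by adding well-recorded early escalations. If these equal 25% of baseline calls, the share falls by up to 17.5 points at p = 0.6 (0.60 − 0.48/1.13), or about 0.18 SD at a 1 SD gap. No section predicts such a rise in calls or gives its size. Only the 20% cut is the protocol's own figure.

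3. *Documentation is not the whole of H5.* Correct. A reader might take D-Catch as the primary measure because H5 is a primary hypothesis, but it is one of three unranked measures. The other two come from staff surveys and do not depend on RRT calls. The limit on scope applies to this one measure.

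4. *Safeguards exist.* Assessors of documentation and deterioration are to be blinded, duplicate records are checked for inter-rater agreement, and the mixed model adjusts for confounders. The blinding and duplicate checks protect the scoring of a given record, and they answer any worry that the same staff may judge both preventability and documentation. They do not change which records enter the sample. Nor does the mixed model as described remove selection on an event that follows the intervention.

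**Conclusion.** The point holds in a limited form. The D-Catch sample is defined by an event that the intervention is expected to change, so the control and intervention records are selected differently. The comparison can be biased, probably towards benefit if H1 holds and preventable calls have poorer records, but the sign is not certain.

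With the protocol's 20% cut alone, an assumed preventable share of 20–60% and an assumed gap of 1 SD, the spurious shift is about 0.03–0.055 SD. On the relative scale it is at most about 4% for deficits up to 50%, so over that range selection would not by itself produce the 10% target. Both the share and the gap are assumptions.

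Whatever the sign of the bias, the score describes only patients with an RRT call, not ward documentation in general. The data source in Table 3 also conflicts with the text. That is a minor correction and would not merit a point alone.

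**What to change.** Draw the same number of D-Catch records at random from study-ward admissions within each cluster and period, stratified by ward and regardless of RRT call. Report any RRT-call records as a separate sample, described as limited to patients with a call. If the RRT-call sample is kept as the main one, add the unselected sample as a sensitivity analysis. Reporting the score by judged preventability would be cheaper, but it still conditions on an RRT call and on a judgement made from the same record.

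Correct the Table 3 data source for Outcome 11 from staff surveys to patient records, to agree with the H5 outcome section and the eMR section.

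Cost: replacing the sample leaves the number of scorings unchanged, while keeping both samples raises it. Unless most of the roughly 4050 admissions a month involve a call, most sampled records would not already be open for H1 review. The measure would also describe ward admissions in general instead of deteriorating patients. Access should not be an obstacle: site research nurses already have eMR access, and the consent waiver covers medical records and progress notes. Recruitment is scheduled to begin in July 2026, so the change can be made before data collection.
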